## Discussion

We have described the rationale and methodology for a multicenter randomized clinical trial to measure the effectiveness of a decision aid on validated patient-centered outcome measures, safety, and healthcare utilization in ED chest pain patients at low-risk for ACS. The trial represents a dynamic and ongoing collaboration between a patient and caregiver representative, the ED patient advisory council at Saint Mary’s Hospital in Rochester (Minnesota, United States), ED clinicians, shared decision-making experts, a cardiologist, and health services researchers and will be the first multicenter shared decision-making trial conducted in an ED setting. If findings from our single-centered randomized trial
[11] are externally validated in a variety of hospital EDs, it will also serve as proof of concept that can subsequently be applied to other emergency conditions and lay the groundwork for future implementation studies to explore how to best incorporate shared decision-making as part of routine clinical care in the emergency setting.

An important reason to conduct feasibility trials of decision aids designed for use in the clinical setting is that the tools have potential to impact the nature and content of the patient-clinician discussion as well as the duration of the clinical evaluation. Although it was not a significant barrier to patient engagement in our pilot trial, patients who present to the ED with chest pain may be in a vulnerable emotional state such that they might prefer decisions be made on their behalf rather than actively participate in their medical care. The ED is also the safety net for patients of all levels of education and for those without medical insurance, and we anticipate that there may be knowledge transfer challenges unique to this practice setting. When clinicians with different practice patterns and levels of experience use the decision aid they may not find it appropriate to use for some patients, or may not use the decision aid appropriately. Therefore, video recording the patient-clinician encounter may provide insight into these potential challenges, the effectiveness of the decision aid, and the nature of the patient-clinician interaction in a busy ED environment.

Randomizing at the patient level increases the risk of contamination between the intervention and control arms. We have taken several steps to minimize the risk of contamination. First, the 45-day ACS risk calculator is password protected and clinicians will not be able to determine an individual patient’s risk of ACS using this instrument, or have access to the decision aid
[16]. Furthermore, in our pilot trial, we observed that when clinicians did not have access to the decision aid and patients’ 45-day risk of ACS, they reverted back to their usual practice of rapid decision-making and limited discussion with patients and were reticent to engage patients in shared decision-making. Second, only the site coordinators will have access to copies of the decision aid, and clinicians will not be provided the decision aid in the usual care arm. Third, site coordinators have been carefully trained to confirm the accuracy of each of the variables needed to generate the 45-day ACS risk estimate by review and sign-off by the treating clinician, but are instructed to keep the clinician blind to a patient’s risk unless a patient is randomized to the decision aid. Fourth, every effort will be made to obtain video and audio data of the disposition discussion in both the intervention and control arms, and we will monitor for contamination by review of these data. Finally, if contamination does occur, we anticipate it will decrease the magnitude of differences observed in the intervention and control groups, biasing the results towards the null.

There are advantages and disadvantages to using two different decision aids in the context of this trial. Having a separate decision aid (Figure 
2) for the site in which coronary CT angiography is routinely used in lieu of cardiac stress testing in low-risk chest pain patients introduces heterogeneity in the intervention. However, a key aspect of contemporary evidence-based medicine involves translating evidence into practice in a manner that is sensitive to local practice context
[30] as well as patients’ values and preferences
[31], and our decision to design two different decision aids reflects an underlying commitment to these values. In addition, a key goal of the decision aid is to generate a conversation about the evidence surrounding a management decision and, by necessity, the conversation must include the management options frequently used in that practice context to be relevant for participating clinicians. Finally, we plan to measure the effect of the intervention both overall and by site, which will provide insight into any differences in effectiveness between sites.

It is possible that not all of the clinicians at each site will be willing to participate in the trial. This has the potential to decrease the rate of recruitment. However, in our pilot trial over 90% of the clinicians at our site agreed to participate
[11], and the majority of the sites participating in the trial have a track record of successfully recruiting ED chest pain patients for prospective research, therefore we anticipate a high degree of clinician support and participation in the study.

In conclusion, this trial will compare the effectiveness of a shared decision-making approach to usual care in patients with low-risk chest pain presenting to the ED for evaluation. Such an approach has the potential to safely tailor advanced cardiac testing to the degree of patient risk in a manner that educates and empowers patients to participate in the decision-making process, is consistent with patients’ values and preferences, and is supportive of clinicians’ knowledge and expertise.

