[13]. One way to think of this is as a fluid process, in which an experienced clinician seamlessly transitions from one decision-making model to the next, depending on the approach that seems most appropriate given the clinical context and the individual patient.

In prior work we developed a decision aid, Chest Pain Choice (CPC),
[14] and tested the hypothesis that use of the decision aid during a clinical encounter would facilitate a shared approach to medical decision-making, improve patient-centered decision-based outcomes (patient knowledge, engagement in the decision-making process and satisfaction), and safely decrease resource utilization. The decision aid described to patients the rationale for their chest pain evaluation and the potential utility of urgent cardiac stress testing. It also included a precise estimate of the 45-day risk for ACS derived from a robustly validated prediction model
[5,15,16] and communicated that risk using prose phrases, numbers, and a pictograph to account for the patient’s preferred mode of understanding numerical information
[14]. In a single-center randomized pilot trial (n = 204) we observed greater knowledge regarding management options and the short-term risk for ACS, greater engagement in the decision-making process, and a 19% lower rate of observation unit admission for cardiac stress testing in patients randomized to this shared decision-making intervention compared to usual care, and there were no major adverse cardiac events within 30 days in either arm
[11].

In this paper we describe the rationale and methods employed to test the effectiveness of the CPC decision aid in a multicenter trial in five geographically and ethnically diverse hospital EDs in the United States. We hypothesize that use of the decision aid will significantly increase patient knowledge, engagement and satisfaction, and decrease the rate of testing that may have marginal benefit in the low-risk population with no increase in adverse events.

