#### Statistical considerations

In order for the study findings to maximally impact practice and policy, they will need to be adequately powered to detect differences in outcomes of interest to each of the stakeholders (patients, clinicians, shared decision-making research experts, and healthcare payers). We will have sufficient funding to enroll 930 patients, accounting for a loss to follow-up rate as high as 5% (there was 2% lost to follow-up in our pilot trial)
[11], we anticipate having complete data on 884 patients. Table 
1 shows the anticipated power we will have to detect differences in each of the patient and stakeholder-important outcomes on completion of the trial.

**Table 1 T1:** Anticipated power to detect patient and stakeholder-important outcomes on completion of the trial

**Outcome (n = 884)**	**Usual Care***	**Decision Aid***	**Difference**	**Power**
**Patient knowledge**	44% (23.3)	60% (20.9)	16% (9.5%, 22.5%)	99%
**Patient engagement in the decision-making process (n = 221)**	7.0 (5.5)	26.3 (8.2)	19.3 (18.4, 20.2)	99%
**Decisional conflict†**	35.9 (18.9)	22.3 (21.1)	13.6 (11.0, 16.2)	99%
**Trust in the physician**	79.3 (19.9)	83.4 (19.8)	4.1 (1.5, 6.7)	86%
**Patient satisfaction with the decision made (% agree or strongly agree they are satisfied)**	69.7 (25.6)	80 (25.6)	10.3 (4.6%, 16.0%)	99%
**Safety (major adverse cardiovascular events)‡**	0%	0%	0% (−−)	78%
**Proportion of patients admitted for cardiac testing**	77%	67%	10% (4.1, 15.9)	90%
**Healthcare utilization**	8.3 (0.8)	7.0 (0.7)	1.3 (1.2, 1.4)	99%

*Estimates were determined from our completed pilot randomized trial [11].

†Lower decisional conflict scores indicate less conflict experienced by patients related to feeling uninformed.

‡Non-inferiority, one-sided test with alpha = 0.05 with a maximum difference of 5%.

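### The article says contamination would bias the results towards the null; for the MACE non-inferiority test that direction is anti-conservative, and the safety reading should be tied to the admission difference

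*Protocol article*

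**What the plan says.** The contamination paragraph of the Discussion concedes that "Randomizing at the patient level increases the risk of contamination between the intervention and control arms". It lists safeguards: a password-protected risk calculator, copies of the aid held only by coordinators, coordinators told to keep clinicians blind to the risk of control patients, and review of recordings. It also reports that pilot clinicians without the aid went back to their usual practice. It ends by saying of any remaining carry-over between arms: "we anticipate it will decrease the magnitude of differences observed in the intervention and control groups, biasing the results towards the null". The statement covers the results in general.

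Under Statistical considerations, Table 1 has a row labelled "Safety (major adverse cardiovascular events", and its footnote reads "Non-inferiority, one-sided test with alpha = 0.05 with a maximum difference of 5" (per cent). It is the only row marked as non-inferiority. The Background hypothesis is that the aid will "decrease the rate of testing that may have marginal benefit in the low-risk population with no increase in adverse events". No other part of the article says that dilution works differently for the safety comparison.

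**The concern.** Allocation is by patient, and the analysis plan expects repeated measures on clinicians, so one clinician can treat patients in both arms. A way of discussing risk learned with aid patients may carry over to later controls even if the printed aid and the calculated risk are withheld.

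For a superiority test, the arms moving together means lost power, and a positive result is still trustworthy. For a non-inferiority test, the null hypothesis is an excess of at least the margin. The arms moving together takes the data away from that hypothesis and towards the conclusion that the aid is no worse. The sentence therefore reassures in the wrong direction for safety.

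At stake is the claim that testing falls without added harm. That claim needs two things: that the arms were managed differently, and that MACE did not rise. If contamination removed the first, the second could still pass its test, although the safety of admitting fewer patients had not been examined.

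**Working it through.** **Inputs from the article**
- Analysed patients: 930 × 0.95 = 883.5. This agrees with "we anticipate having complete data on 884 patients". At 1:1 allocation that is 442 per arm.
- Safety test: one-sided alpha 0.05 (z = 1.645), margin 5 percentage points.
- Admission: 77% against 67%, stated power 90%.

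**Assumptions, not in the article**
- MACE in uncontaminated controls: 1%. The pilot gives no usable rate, since "there were no major adverse cardiac events within 30 days in either arm"; 0% to 2% is tried below.
- Carry-over c: the share of the aid's effect that reaches controls. If the true excess is e, the aid rate is 1% + e and the observed control rate is 1% + c × e.

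**The plan's own figures first.** Admission power, normal approximation with pooled variance under the null: SE0 = √(2 × 0.72 × 0.28/442) = 0.0302 and SE1 = √((0.77 × 0.23 + 0.67 × 0.33)/442) = 0.0300. Power = Φ((0.10 − 1.96 × 0.0302)/0.0300) = 91%, in line with the stated 90%. The stated 78% power for MACE does not reproduce from 0% against 0%: the variance is then zero and the formula gives 100%. A common rate of about 10.6% would be needed to obtain 78%. That is a separate matter and does not affect this point.

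**False non-inferiority with the true excess at the margin (e = 5 points, aid rate 6%).**
P(declare) = Φ((0.05 − d)/SE − 1.645), where d is the difference after carry-over and SE = √((pC(1 − pC) + pA(1 − pA))/442).

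For c = 20%: pC = 2%, pA = 6%, d = 4 points, SE = √((0.0196 + 0.0564)/442) = 0.0131. Then (0.05 − 0.04)/0.0131 = 0.763, and Φ(0.763 − 1.645) = 18.9%.

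| Carry-over | Observed control rate | Normal approximation | Exact enumeration of the same Wald rule | Power, admission |
|---|---|---|---|---|
| 0% | 1.0% | 5.0% | 6.5% | 91% |
| 10% | 1.5% | 10.5% | 12.3% | 84% |
| 20% | 2.0% | 18.9% | 20.6% | 75% |
| 30% | 2.5% | 29.6% | 30.9% | 63% |

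The admission column sets the usual-care rate to 77% minus c × 10 points. The two error columns and the power column move in opposite directions for inference: contamination is conservative for admission and anti-conservative for MACE. Over uncontaminated control rates of 0% to 2%, c = 20% gives 17% to 22% by the normal approximation.

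**Smaller true excesses (1% base, same formula), chance of declaring non-inferiority**
- e = 1 point: 99.9% at c = 0, and still above 99.9% at c = 30%.
- e = 2 points: at c = 0, SE = √((0.0099 + 0.0291)/442) = 0.0094 and Φ(0.03/0.0094 − 1.645) = 94%. At c = 30%, pC = 1.6%, d = 1.4 points, SE = 0.0101 and Φ(0.036/0.0101 − 1.645) = 97%.

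These excesses lie inside the margin, so declaring non-inferiority is not an error by the plan's own standard. For scale, 0 events in 442 has a one-sided 95% upper bound of 1 − 0.05^(1/442) = 0.68%, far below 5 points.

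**The case against.** The strongest reply is that the inflated error rates describe a remote case. Table 1 expects admissions to fall by 10 points. If harm came only through those avoided admissions, a 5-point excess of MACE would mean an event in about half of the additional patients sent home (5/10). These are patients described as very low-risk, randomised after a negative first troponin, and the pilot saw no MACE. This stands: the figures are a worst case, and the 5-point margin is the larger weakness of the safety test. It does not make the direction of the sentence right.

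Three stronger readings are tempting, and the article does not support them.
- A reader might infer that the article calls contamination harmless, or that the one-sided 5% error fails under any carry-over. The article says only that differences shrink, which is literally true for MACE too. The error is inflated only when the true excess is at or beyond the margin, by an amount that depends on an assumed fraction. The one piece of evidence given, from the single-centre pilot, points to low carry-over.
- A reader might infer that the sentence also disposes of non-use of the aid. It does not. The Discussion raises separately that clinicians may differ, and that "they may not find it appropriate to use for some patients, or may not use the decision aid appropriately"; it makes no claim there about the direction of bias.
- A reader might infer that nothing shows whether the arms were managed differently. In fact admission is a named outcome, advanced testing is taken from the medical record, recordings are used to assess fidelity and contamination, and intra-clinician correlation is assessed. Recording is optional, but admission and testing data do not depend on it. What the article lacks is a rule that links these to the safety conclusion.

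It can also be said that such a rule belongs in a full protocol or analysis plan that is not shown. Its absence alone would be no finding. The finding is the unqualified sentence that the article does print; the rule is part of the remedy.

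**Conclusion.** The point holds in a limited form. The statement on contamination is right for the superiority outcomes and points the wrong way for the MACE non-inferiority test, and nothing else in the article corrects it. At the margin, assumed carry-over of 10% to 30% raises the false non-inferiority rate from 5% to between about 11% and 30%. This rests on 442 per arm, 1% control MACE, a true excess of exactly 5 points, and carry-over fractions that the article does not give. At excesses of 2 points or less the chance of declaring non-inferiority is already 94% or more without carry-over, so contamination adds little. The practical consequence is one of interpretation: a non-inferior MACE result does not by itself show that admitting fewer patients is safe, because it would also be expected if the arms had been managed alike.

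**What to change.** 1. Limit the sentence in the Discussion to the superiority outcomes, and add that contamination is anti-conservative for the MACE non-inferiority test.
2. Pre-specify that non-inferior MACE is read as support for a safe reduction in admissions only when the admission difference is itself shown. Otherwise, report that the safety of admitting fewer patients was not tested.
3. Optionally, as an exploratory analysis adjusted for site and calendar time, relate admission among usual-care patients to the number of aid-arm patients their clinician had treated before, and report it beside the safety result. Without adjustment this slope is confounded with calendar time, and it also depends on which clinicians enrol often, so it cannot serve as a formal test of carry-over.

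The cost is a change of wording and, if wanted, one regression using randomisation order and clinician identity. Design, sample size and patient care are unchanged. The downside is that non-inferior MACE without an admission effect can no longer be presented as proof of a safe reduction.

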## Trial status

The study began enrolling patients in October 2013.

## Abbreviations

ACS: Acute coronary syndrome; AMI: acute myocardial infarction; CAD: coronary artery disease; CPC: chest pain choice; CT: computed tomography; DSMB: data safety monitoring board; ECG: electrocardiography; ED: Emergency department; EM: Emergency medicine; THE: heterogeneity of treatment effect; MACE: Major adverse cardiac events; OPTION: observing patient involvement; QPTP: Quantitative pretest probability; REDCap: Research electronic data capture; UB: universal billing.
